#### Activation analysis of fNIRS

The preprocessed hemodynamic data will be subjected to a standard activation analysis to identify brain regions exhibiting significant task-related responses. The final model specifications and statistical thresholds will be determined based on the data quality and standard practices in the field.

#### Functional connectivity of fNIRS

Functional connectivity (FC) is evaluated by calculating the temporal sequence correlation between different brain regions. The specific metric for quantifying FC (e.g., Pearson’s correlation, phase-based connectivity) and the approach for statistical validation (e.g., Fisher’s z-transformation, permutation testing) will be selected based on the properties of the final processed data.

### Expectation and credibility

Before the first treatment session, the expectation questionnaire will be used to assess the patients’ expectations. Expectation will be measured using the NRS scale, where 0 indicates complete lack of expectation and 10 signifies the maximum expectation. After the final treatment session, the credibility questionnaire will be used for assessment. The credibility scale assesses acupuncture-induced confidence change in itch relief using a 5-point scale ranging from −2 to 2, where −2 indicates “marked decrease,” −1 indicates “mild decrease,” 0 indicates “no change,” 1 indicates “mild increase,” and 2 indicates “marked increase.”

### Adverse events

In case of any adverse event, researchers should immediately stop intervention, take appropriate emergency measures, and meticulously record the time, location, symptoms, severity, handling measures, and outcome of the event. The researchers will examine the causes and evaluate the causal relationship with the intervention.

### Statistical analysis

All statistical analyses will be performed using the IBM SPSS Statistical software package version 26 (IBM, Chicago, IL, USA). All the numerical data will be presented in the form of average values and standard deviations, and will be analyzed using the independent t-test or Mann–Whitney U test. The categorical data will be expressed as number (n) and percentage (%), and the differences between groups will be compared using the Chi-square. The preprocessing and analysis of fNIRS data will be carried out using NirSpark (Danyang Huichuang Medical Equipment Co. Ltd., China).

A two-sample *t*-test will be conducted to compare the brain activation and functional connectivity between the verum acupuncture and the sham acupuncture groups. All statistical tests will use a significance level of 0.05, with corrections for multiple comparisons.

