#### Sample size

Based on the observed change in itch NRS (numeric rating scale) scores from the pilot experiment (verum acupuncture group: 2.86 ± 1.07 VS sham acupuncture control group: 2.00 ± 0.58). With 80% statistical power, a 5% significance level, and accounting for a projected 20% dropout rate. Each group requires 20 people, and a total of 40 subjects need to be recruited. The calculation was performed using an *a priori* power analysis conducted with G*Power software (version 3.1), based on a t-test for the difference between two independent means (35).

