#### Primary outcomes

The primary outcome was defined as the change of the itch NRS score, calculated by subtracting the post-intervention score from the baseline score. The intensity of itch will be evaluated using the NRS. The NRS is a patient-reported instrument in which subjects rate their subjective itch intensity on a numerical scale anchored at 0 (“no itch”) and 10 (“worst imaginable itch”). Measurements will be conducted at pre-acupuncture resting state, intervention period, and post-acupuncture resting state.

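### The primary itch NRS change is to be compared without adjusting for baseline NRS; the planned test is valid, but baseline-adjusted ANCOVA would be a free gain in precision

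*Protocol article*

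**What the plan says.** The Primary outcomes section of the protocol article fixes the endpoint: "The primary outcome was defined as the change of the itch NRS score, calculated by subtracting the post-intervention score from the baseline score". The same section confirms that the baseline value will be available: "Measurements will be conducted at pre-acupuncture resting state, intervention period, and post-acupuncture resting state".

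The Statistical analysis section gives one rule for all numerical data, which "will be analyzed using the independent t-test or Mann–Whitney U test". The article describes no model with baseline NRS as a covariate.

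The Sample size section is consistent with this. It works from pilot changes ("verum acupuncture group: 2.86 ± 1.07 VS sham acupuncture control group: 2.00 ± 0.58") and is "based on a t-test for the difference between two independent means". Its other inputs are: "With 80% statistical power, a 5% significance level, and accounting for a projected 20% dropout rate". Its result is: "Each group requires 20 people, and a total of 40 subjects need to be recruited".

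The Randomization and allocation concealment section describes 1:1 allocation and mentions no stratification on baseline itch.

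**The concern.** A change score is not independent of its own baseline. People who score high before treatment tend to fall further by regression to the mean, whatever they receive. Subtracting the baseline therefore removes a between-arm baseline difference completely only if the post score rises one for one with the baseline score. If the slope is below one, the remainder of a chance imbalance stays in the estimated treatment effect, and the variance of the change score is larger than it need be.

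Both effects matter more in a small trial. Here each arm has 20 people, or 16 if the projected dropout occurs, and randomisation is not described as balancing baseline itch. Entry requires a weekly average NRS of at least 4, so baseline can still vary over much of the upper scale. The adjustment variable is already being collected, so any precision lost on the primary clinical endpoint is lost for no saving.

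**Working it through.** **Inputs from the Sample size section.** Pilot change: 2.86 (SD 1.07) verum, 2.00 (SD 0.58) sham. Power 80%, alpha 5% (two-sided assumed, since sidedness is not stated), dropout 20%, 20 per arm.

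**Inputs not in the article, so assumed.** Baseline NRS SD *s*, taken from 1.0 to 2.0; equal SDs before and after acupuncture. The pre-post correlation *r* then follows from *s* and the pilot change SD.

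**1. Reproduce the planned size.**
- Difference = 2.86 − 2.00 = 0.86.
- Pooled SD of change = √((1.07² + 0.58²)/2) = 0.861, so *d* = 0.86/0.861 = 1.00.
- Normal approximation: 2 × (0.861 × (1.960 + 0.842)/0.86)² = 15.7, rounded up to 16; 16/0.8 = 20 per arm, which is the stated figure.

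**2. Power of the planned analysis.** Using the noncentral *t* distribution, the unadjusted two-sided t-test on change has 78.1% power with 16 evaluable per arm and 86.8% with 20.

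**3. Tie the correlation to the pilot SD.** With equal SDs, Var(change) = 2*s*²(1 − *r*). Fixing this at 0.861² = 0.741 gives *r* = 1 − 0.741/(2*s*²):
- *s* = 1.0: *r* = 1 − 0.741/2 = 0.63
- *s* = 1.5: *r* = 1 − 0.741/4.5 = 0.835
- *s* = 2.0: *r* = 1 − 0.741/8 = 0.91

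**4. Power with ANCOVA.** The residual variance is *s*²(1 − *r*²), so its ratio to the change-score variance is (1 + *r*)/2. Power uses the noncentral *t* with 2*n* − 3 degrees of freedom, *n* = 16 per arm.

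**5. Shift from a chance imbalance.** A baseline difference of one standard error, *s*√(2/20) with 20 per arm, moves the unadjusted difference in change by (1 − *r*) times that amount. For *s* = 1.5: 1.5 × √0.1 = 0.474, and 0.165 × 0.474 = 0.08.

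| Assumed baseline SD | Implied *r* | Variance ratio | ANCOVA power, 16 per arm | Unadjusted power, 16 per arm | One-SE shift, 20 per arm | Share of 0.86 |
|---|---|---|---|---|---|---|
| 1.0 | 0.63 | 0.81 | 85.7% | 78.1% | 0.12 | 14% |
| 1.5 | 0.835 | 0.92 | 81.4% | 78.1% | 0.08 | 9% |
| 2.0 | 0.91 | 0.95 | 79.9% | 78.1% | 0.06 | 7% |

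The gain is therefore about 2 to 8 percentage points of power. If change is unrelated to baseline, the variance ratio is 1, the gain is nil, and ANCOVA costs one degree of freedom.

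**The case against.** The strongest reply is that nothing here is wrong. In a randomised trial a two-sample t-test on change keeps its type I error and is unbiased on average, and the change score already removes part of any baseline difference. Endpoint, sizing test and analysis test all agree. This stands: a reader might infer that the planned comparison is biased or invalid, and the document does not support that.

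The gain may also be small. Ratings are taken within one session of three consecutive 5-minute epochs, and entry requires relatively stable itch, so a high pre-post correlation is plausible. This stands too, and it points towards the lower rows of the table. The article also calls the study a pilot giving preliminary insight, which limits how much hangs on a few points of power.

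Two stronger readings are tempting and do not hold.

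- **A much larger effect of adjustment.** Pairing a baseline SD of 1.5 with a correlation of 0.5 gives a shift of 0.474 × 0.5 = 0.24 points, 28% of 0.86. Under equal variances those two values imply a change SD of √(2 × 1.5² × 0.5) = 1.5, which contradicts the pilot 0.861 on which power is calculated. Similarly, ANCOVA power of 88% or 92% with 16 per arm needs correlations of 0.5 or 0.3, which imply baseline SDs of only 0.86 or 0.73, below the range assumed here.
- **A primary test left open to choice after the data are seen.** The two-test wording is a general sentence about all numerical data, and the Sample size section points to the t-test for the primary comparison. The rule for moving to the rank test is detail that an article may leave to the full protocol or SAP.

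A missing SAP does not dispose of the main point. The article positively names unadjusted tests and sizes the trial on one of them, so this concerns a stated choice, not an omission.

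**Conclusion.** The point holds as an efficiency and conditional-bias improvement to a valid analysis. On inputs consistent with the pilot change SD, adjustment brings the 16-per-arm trial from just under its 80% target to about that target or modestly above it, and it removes the exposure to baseline imbalance sized in the table. These figures rest on an assumed baseline SD of 1.0 to 2.0, equal SDs before and after, a linear relation with a common slope, and two-sided testing. None of these can be checked from the article, and the pilot change SDs differ between arms, so the table shows a plausible range and is not a prediction. The change is worth making because it is nearly costless, not because the planned test fails.

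**What to change.** State in the Statistical analysis section that the primary analysis is an ANCOVA (linear model) of post-acupuncture NRS on treatment arm and pre-acupuncture NRS, two-sided 0.05, reporting the adjusted mean difference with its 95% CI. Heteroscedasticity-robust standard errors are reasonable given pilot SDs of 1.07 and 0.58. Keep the unadjusted comparison of change as a sensitivity analysis.

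The cost is about one sentence of text and one residual degree of freedom. No new data, visits or participants are needed. Using the change score as the response in the same model gives the identical treatment effect apart from sign, so the endpoint definition ("calculated by subtracting the post-intervention score from the baseline score") can stay as it is.

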### Data management and quality control

Standardized training shall be implemented for all researchers to ensure comprehensive understanding of the study objectives and protocol requirements. All researchers are required to achieve comprehensive proficiency in the study protocols, including the application of diagnostic criteria, implementation of treatment protocols, execution of randomization procedures, administration of standardized acupuncture techniques, and proper utilization of assessment tools. All the acupuncturists involved in this project have obtained the physician qualification certificates and have received standardized training. Uniformly printed Case Report Forms (CRFs) shall be used to standardize all research documentation. Protocol adherence will be rigorously maintained to guarantee the timely, objective, and accurate completion of all CRFs. Upon review and approval by the quality inspector, the document shall be transferred to the designated data entry clerk for input and storage.

Currently, neuroimaging research on acupuncture’s effect remains limited, particularly regarding the neural mechanisms underlying acupuncture treatment for chronic itch, which have not been systematically investigated. The exploration of immediate anti-pruritic effects of acupuncture may help reduce potential confounding factors from cumulative treatment effects and provide insights into acupuncture’s acute neuromodulatory responses. Given this knowledge gap, there is a need for exploratory studies to provide preliminary insights into the immediate neuromodulatory effects of acupuncture on core brain regions implicated in chronic itch.

fNIRS offers complementary advantages for intervention studies, including high temporal resolution, portability, and reduced susceptibility to motion artifacts and metal implants, providing significant advantages in clinical applications (30). Its ability to reliably monitor the hemodynamic activity of the superficial cortex makes it ideally suited to capture the dynamic neural responses within the prefrontal and motor regions during acupuncture treatment for itch.

This pilot study employs fNIRS to simultaneously evaluate acute clinical responses and underlying neural mechanisms, providing initial evidence for acupuncture’s potential regulatory effects on central itch processing pathways. Specifically, the present study focuses on the immediate (short-term) neural effects of a single acupuncture session, as captured in real time by fNIRS during treatment. This design enables us to identify transient cortical hemodynamic changes that accompany rapid symptom relief, thereby offering a unique perspective distinct from studies emphasizing long-term or cumulative effects of repeated interventions. By integrating real-time neuroimaging with concurrent clinical assessment, we will achieve preliminary quantification of immediate improvements in patients’ itch symptoms alongside corresponding neural mechanism analysis. Understanding these immediate central mechanisms is crucial for elucidating how acupuncture exerts its antipruritic effect at the onset of treatment, before chronic adaptations occur.

Several limitations should be acknowledged. First, the tactile nature of needling precluded blinding of acupuncture practitioners, potentially introducing performance bias despite rigorous assessor blinding. Second, as a pilot investigation focused on immediate effects, this study will not assess long-term therapeutic outcomes or provide comprehensive exploration of underlying neural mechanisms. Third, due to the limited coverage of the neuroimaging equipment, the acquired data will be restricted primarily to the prefrontal cortex and motor-related areas. Fourth, although fNIRS has lower spatial and temporal resolution compared to fMRI and Electroencephalogram/Magnetoencephalography, its practical advantages—portability, motion tolerance, and compatibility with acupuncture procedures—make it the optimal choice for investigating immediate cortical responses in naturalistic settings.

## Conclusion

As this paper presents a study protocol rather than completed results, our work aims to explore the immediate neural mechanism of acupuncture in treating itch based on fNIRS, providing a scientific basis for the precise diagnosis and treatment of chronic itch.

## Data Availability

The original contributions presented in the study are included in the article/supplementary material, further inquiries can be directed to the corresponding authors.
